## Methods/design

### Objectives

The primary objective of this study is to evaluate whether ISBCS is non-inferior to DSBCS regarding effectiveness, where effectiveness is defined as the proportion of patients with a postoperative refraction that deviates ≤1 D from target refraction. Secondary objectives of this study are to evaluate ISBCS versus DSBCS regarding non-inferiority of (1) the proportion of patients with a postoperative refraction within 0.5 D of target refraction, and (2) postoperative visual acuity, and superiority of (3) patient satisfaction (using patient reported outcome measures (PROMs)), (4) the incidence of complications, and (5) cost-effectiveness.

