### Outcome measures

The primary outcome is the proportion of patients in both treatment groups with a postoperative refraction in the second eye that deviates ≤1.0 D from target refraction 4 weeks after cataract surgery of the second eye. This is an accepted norm to define success in terms of refractive outcomes after cataract surgery [7, 28].

Secondary outcomes will include:
**Refraction**: the proportion of patients in both treatment groups with a postoperative refraction in the second eye that deviates ≤0.5 D from target refraction 4 weeks after cataract surgery of the second eye.**Visual acuity**: ETDRS, uncorrected and corrected distance visual acuity in LogMAR (the Logarithm of the Minimum Angle of Resolution), 1 week after first-eye surgery and 4 weeks after second-eye surgery, corrected for baseline visual acuity. In addition, the proportion of patients with a final corrected distance visual acuity (CDVA) of ≤0.1 LogMAR (measured at 4 weeks after second-eye surgery) will be compared for ISBCS and DSBCS.**Complications**: the number of intraoperative and postoperative complications within 3 months after first-eye surgery.**Patient-reported outcome measures (PROMs)**, including patient satisfaction, vision-specific quality of life, and health-related quality of life:

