Vision-specific quality of life and patient satisfaction will be measured using the National Eye Institute Visual Function Questionnaire-25 (NEI VFQ-25) [37] and the Catquest-9SF [38], measured at baseline and 3 months after first-eye surgery (Table 1).Health-related quality of life (HRQL) will be measured using two questionnaires: EuroQol’s EQ-5D-5L [39] and the Health Utilities Index Mark-3 (HUI-3) [40], measured at baseline, 1 week after first-eye surgery, 4 weeks after second-eye surgery and 3 months after first-eye surgery (Table 1).**Incremental cost-effectiveness ratios (ICERs)**: these will be expressed as 1) incremental societal costs per quality-adjusted life year (QALY) gained, 2) incremental healthcare costs per patient with postoperative refraction ≤1.0 D from target refraction, 3) incremental healthcare costs per clinically improved patient on the NEI VFQ-25 questionnaire, 4) incremental healthcare costs per clinically improved patient on the Catquest-9SF questionnaire, and 5) incremental healthcare costs per patient with clinical improvement in (un)corrected distance visual acuity. QALYs will be calculated based on generic HRQL.**Budget impact** will be reported as a difference in costs. Different scenarios will be compared to investigate the impact of various levels of implementation.

Adverse events are defined as any undesirable ophthalmic event occurring during the study, whether or not considered related to the trial procedure or the experimental intervention. All ophthalmic adverse events reported spontaneously by the patient or observed by the investigator or his staff will be recorded. Serious adverse events are defined as any untoward medical occurrence or effect that results in death, is life threatening (at the time of the event), requires hospitalisation or prolongation of existing inpatients’ hospitalisation, results in persistent or significant disability or incapacity, is a congenital anomaly or birth defect, or any other important medical event that did not result (but could have resulted) in any of the outcomes listed above due to medical or surgical intervention.

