### Statistical analysis

All data will be collected in a database (Castor) and will be exported to IBM SPSS Statistics (IBM, Armonk, NY, USA) for data analysis. The data analyses will be performed according to the intention to treat principle. However, considering that second-eye surgery can be delayed in ISBCS patients with complications during first-eye surgery, the analyses will be repeated based on a per protocol analysis. As recommended for non-inferiority trials in literature, both analyses will be performed and non-inferiority will be established if both analyses produce the same conclusion [42]. For all analyses, stratification variables (center and axial length) are accounted for by including them in the analysis model and significance levels will be set at 0.05.

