#### Secondary outcomes

For secondary outcomes, data analyses will be performed as follows: presence of non-inferiority of ISBCS compared to DSBCS regarding the difference in the proportion of second eyes with a refractive outcome within ±0.5 D of target refraction will be evaluated similar to the method described under primary outcome. For visual acuity, presence of non-inferiority of ISBCS will be evaluated by comparing the proportion of patients with a corrected distance visual acuity (CDVA) 4 weeks after surgery of the second eye of ≤0.10 LogMAR between groups. The computed sample size of 858 patients for the primary outcome translates to an allowed non-inferiority margin of 10% to establish non-inferiority at the 0.05 alpha level regarding this secondary outcome measure. Corrected and uncorrected distance visual acuity in second eyes, patient-reported outcomes, and utilities will be analysed using a linear mixed model to test for overall differences between groups over time. The difference in the incidence of intraoperative and postoperative complications will be analysed using mixed-effects logistic regression to account for the fact that both eyes of each patient are included in the analysis and nesting of patients within centers.

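### The mixed model for patient-reported outcomes leaves open the tested term and the role of baseline, although NEI VFQ-25 and Catquest-9SF have one post-surgery reading; a baseline-adjusted 3-month comparison is more precise on either main reading

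*Protocol article*

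**What the plan says.** All of this is in the protocol article.

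- **Objectives:** the aim for these outcomes is "superiority of (3) patient satisfaction (using patient reported outcome measures (PROMs"), so the question is whether patients score better after ISBCS than after DSBCS.
- **Outcome measures and Table 1:** NEI VFQ-25 and Catquest-9SF are "measured at baseline and 3 months after first-eye surgery (Table 1"). That is one reading before surgery and one after.
- **Outcome measures and Table 1:** EQ-5D-5L and HUI-3 are "measured at baseline, 1 week after first-eye surgery, 4 weeks after second-eye surgery and 3 months after first-eye surgery". That is one reading before surgery and three after.
- **Secondary outcomes:** one sentence covers distance visual acuity, the questionnaires and the utilities: "patient-reported outcomes, and utilities will be analysed using a linear mixed model to test for overall differences between groups over time".
- **Outcome measures, visual acuity:** acuity is to be "corrected for baseline visual acuity". No such words are attached to the questionnaires or utilities.
- **Statistical analysis:** for every analysis, "stratification variables (center and axial length) are accounted for by including them in the analysis model", and "significance levels will be set at 0.05".

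The article does not say whether the tested term is the group main effect or the group-by-time interaction, or whether the baseline score is an outcome or a covariate.

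**The concern.** The sentence suits visual acuity, which has two post-surgery readings and a stated baseline correction. It suits the two vision questionnaires less well. They have a single post-surgery reading, so they have a time dimension only if the pre-surgery score is counted as an outcome.

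If it is counted, and the overall group effect is what gets tested, the quantity estimated is the average of two differences. One is the pre-surgery difference, which is zero in expectation because of randomisation. The other is the 3-month difference, which is what the superiority objective concerns. Type I error is kept, so nothing in the output would reveal the problem. A real benefit could be reported as absent, with an estimate half its proper size.

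If the interaction is tested instead, the result is a valid comparison of change from baseline. That still makes less use of the baseline score than adjusting for it would.

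**Working it through.** **The plan's own figure.** The article gives no power, effect size, SD or correlation for any patient-reported outcome. Its only sample size is for the primary endpoint (Sample size calculation: 94% in both arms, margin 5 points, alpha 0.05, power 90%). With one-sided 0.05:

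n = (1.645 + 1.282)² × 2 × 0.94 × 0.06 / 0.05² = 386.4 per arm

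This agrees with the stated 386, and 772 / 0.90 = 858. I use 386 per arm below as the number evaluable.

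**Assumptions not in the article.** Two-sided 0.05 for these outcomes; equal SD of 1 at both readings; no pre-surgery difference between arms; a true 3-month difference of D in SD units; a baseline-to-3-month correlation of r.

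**Three candidate tests.** The standard error is SD × √(2/386) = SD × 0.0720, and power is Φ(effect/SE − 1.96).

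| Test | Effect estimated | SD |
|---|---|---|
| Overall group effect, baseline as an outcome | (0 + D)/2 = D/2 | √((1 + r)/2) |
| Group-by-time (change from baseline) | D | √(2(1 − r)) |
| 3-month score adjusted for baseline | D | √(1 − r²) |

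**Worked case, D = 0.25 and r = 0.5.**

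- Overall: SD = 0.866, SE = 0.0623, z = 0.125/0.0623 = 2.005, power 52%.
- Change: SD = 1, SE = 0.0720, z = 0.25/0.0720 = 3.47, power 93.5%.
- Adjusted: SD = 0.866, SE = 0.0623, z = 0.25/0.0623 = 4.01, power 98%.

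**Range.**

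| D | r | Overall | Change | Adjusted |
|---|---|---|---|---|
| 0.20 | 0.3 | 41% | 65% | 83% |
| 0.20 | 0.5 | 36% | 79% | 89% |
| 0.20 | 0.7 | 33% | 95% | 97% |
| 0.25 | 0.3 | 58% | 84% | 95% |
| 0.25 | 0.5 | 52% | 93.5% | 98% |
| 0.25 | 0.7 | 47% | 99.4% | 99.8% |
| 0.40 | 0.5 | 89% | about 100% | about 100% |

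**The same comparison without fixing D.** Choose D so that the adjusted test has 80% power.

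| r | Overall | Change |
|---|---|---|
| 0.3 | 38% | 62% |
| 0.5 | 29% | 68% |
| 0.7 | 19% | 73% |

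**Why the ordering does not depend on the assumed values.** The ratio of z for the overall test to z for the adjusted test is √((1 − r)/2), which is below 1 for any r above −1. The variance of the adjusted test relative to the change test is (1 − r²)/(2(1 − r)) = (1 + r)/2, which is below 1 for any r below 1. The size of the gain depends on D and r, but its direction does not.

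**Simulation check.** With r = 0.5 and 4,000 simulated trials per setting, rejection rates (overall / change / adjusted) were about 5% each at D = 0. At D = 0.25 they were 51% / 93% / 98%, and the mean estimates were 0.124 / 0.250 / 0.250.

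**Utilities.** EQ-5D-5L and HUI-3 have three post-surgery readings in four. An overall effect that counts baseline as an outcome would be 3/4 of the post-surgery difference if that difference were constant across visits.

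**The case against.** A reader might infer that the plan forces the pre-surgery score into the outcome, so that the effect is necessarily halved and about half the power lost. The documents do not support that.

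- A difference between groups over time is ordinary wording for a group-by-time test. With two readings, that is the between-arm difference in change, and nothing is halved.
- A linear mixed model need not have repeated readings. A model of the 3-month score with center as a random effect and baseline as a covariate is also one, and the article uses mixed models elsewhere for patients nested in centers.
- The context leans away from the harmful reading. Visual acuity, in the same sentence, is baseline-corrected, and the cost-effectiveness ratios use clinical improvement on both vision questionnaires.
- No single figure for the power loss can be read from the article. It depends on an effect size and correlation that are not given; at 0.40 SD and r = 0.5 the gap is only 89% against about 100%.
- The 75% figure for utilities needs a constant effect. That is unlikely, since one week after first-eye surgery DSBCS patients have only one operated eye. The superiority objective also names patient satisfaction, not utilities.

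All of this stands. It can also be said that a condensed article may leave the tested term to the full protocol (version 7.0, not shown) or the analysis plan. That carries part of the way. But the article does not simply stay silent: it names a model and a hypothesis for these outcomes, and states baseline correction for one outcome in the group and not the others. Even on the favourable group-by-time reading, a more precise analysis is available from data already collected.

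**Conclusion.** The point holds as a worthwhile improvement to a secondary analysis, not as proof of a biased one. The stated analysis fits a two-reading questionnaire poorly and admits two main readings.

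- **Overall group effect with baseline as an outcome:** the estimate is exactly half the 3-month difference, and power drops sharply.
- **Group-by-time:** the test is valid and the effect is intact. The cost is precision only, moderate at r = 0.5 and small at r = 0.7.

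If the intended model already has baseline as a covariate, only the wording needs to change.

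The halving follows from randomisation alone. The power figures rest on 386 evaluable patients per arm, two-sided 0.05, equal SDs and assumed values of D and r, so they are illustrations. The primary outcome, its margin and the sample size are not affected.

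**What to change.** Under Secondary outcomes, separate the questionnaires and utilities from the shared sentence and state the analysis for each.

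- **NEI VFQ-25 and Catquest-9SF:** compare the 3-month score between arms in a linear model adjusted for baseline score, center and axial length.
- **EQ-5D-5L and HUI-3:** use the post-surgery readings as outcomes in the mixed model, with baseline utility as a covariate, or keep baseline in the model with the arm means constrained equal at that visit. Report the arm difference at each visit, so that a difference varying between visits is visible.

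This brings these outcomes into line with the baseline correction already stated for visual acuity. It costs one or two sentences and needs no new data or patients, because the baseline scores are already collected. The constrained-baseline form also keeps patients whose baseline score is missing.

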#### Cost-effectiveness analysis

A trial-based economic evaluation will be performed over a three-month time horizon (first-eye surgery until the final questionnaires at 3 months after first-eye surgery). A societal and healthcare perspective will be used and ICERs will be calculated for the outcome measures described earlier in this protocol. Uncertainty in the point estimates of the ICERs will be assessed using bootstrap analyses with 1000 replications. Based on these bootstrap analyses, cost-effectiveness acceptability curves will be constructed, to show the probability that the intervention is cost-effective for a range of threshold values of the ICER. Additional sensitivity analyses will be performed to investigate the impact of varying input parameters used in the cost-effectiveness analysis.

In addition to the trial-based economic evaluation, the lifetime economic impact of ISBCS compared to DSBCS will be investigated by means of a decision analytical model, in order to take rare events (e.g. bilateral complications) into account. The model-based economic evaluation will address the cost per QALY (societal perspective) and cost per patient with postoperative refraction within 1.0 D from target refraction (health care perspective). Input data for the model will be based on the data from the current study and from a literature review. We will express the model’s robustness and uncertainty by means of sensitivity analyses, confidence intervals, and by creating cost-effectiveness acceptability curves. Annual discount rates of 4 and 1.5% for costs and QALYs, respectively, will be used to determine the present value of costs and QALYs accrued over a lifetime.

In accordance with the Dutch guidelines for economic evaluations, the EQ-5D-5L will be used to determine QALYs using published Dutch tariffs [39]. In addition, the HUI-3 will be used because it is the only generic preference-based HRQL questionnaire that includes questions about vision [40].

For the cost analysis, all relevant costs incurred during the follow-up period from a healthcare and societal perspective will be included. Hospital-based resource use will be identified through patients records. Other resource use (e.g., use of homecare, costs of spectacles, productivity losses) will be measured through the standardized cost questionnaire at baseline and at 3 months after first-eye surgery. Resource use will be valued in accordance with the Dutch guidelines for costs analyses [44]. All costs will be adjusted for inflation to a common price level using the Consumer Price Index.

#### Budget impact analysis

A budget impact analysis (BIA) will be performed to evaluate the impact of implementation of ISBCS on the Dutch healthcare budget. The BIA will be performed in accordance with the Dutch guidelines for economic evaluations and the ISPOR guidelines [45, 46]. The analysis will make use of the budget holder perspective. Additional perspectives include healthcare providers and insurers. A time horizon of 3 years will be used to account for gradual implementation of ISBCS. The BIA will be performed using a simple Microsoft Excel decision analytic model. It will be assumed that the difference in costs will be related completely to substitution of DSBCS by ISBCS. Different scenarios will be compared to investigate various levels of implementation (i.e., 25, 50, 75, and 100% of eligible patients). Sensitivity analyses will be performed to test the robustness of the analysis.

### Data management and monitoring

Personal data will be handled confidentially, according to Good Clinical Practice guidelines (GCP). Data will be collected in an online case report form (CRF), available in the certified electronic data capture tool ‘Castor’ by a member of the study team of each study center. All data will be stored and analysed using only anonymous randomization numbers. Personal data connecting a patient to the anonymous number will be archived by the principal investigator of each study center for a period of 15 years. This study will be monitored by the Clinical Trial Center Maastricht (CTCM) in order to protect patient rights and accuracy of reported trial data. The CTCM is an academic research organisation, familiar with monitoring procedures.

## Discussion

Worldwide, an increasing number of cataract surgeries is performed over the years and healthcare expenditures are rising. Therefore, small efficiency gains in cataract care delivery, such as those potentially gained in ISBCS, may lead to substantial cost savings on a macro level. ISBCS is increasingly practiced on a routine basis in a number of countries around the world, including Finland, certain regions in Spain, and Canada [47]. Potential benefits of ISBCS include less time between surgeries, fewer hospital visits, a faster total recovery period due to simultaneous postoperative care (eye drops) in both eyes and less use of homecare. As a consequence of the recent COVID-19 crisis we now face a scenario where the number of hospital visits, if feasible, should be decreased to diminish the risk for contamination in the hospital. ISBCS could be an instrument to significantly decrease residence time of patients in the clinic for surgery as well as for postoperative controls. However, opponents of ISBCS argue that the potential risks of severe bilateral complications and unexpected refractive outcomes supersede any economic arguments [48]. The main concerns about ISBCS include potential risks of bilateral complications of cataract surgery, most importantly the very rare but severe risk of endophthalmitis and the risk of refractive surprise (a significant deviation from the predicted refraction).

Further investigation is required to evaluate how ISBCS compares to DSBCS with respect to cataract surgery outcomes, in particular with regard to refractive outcomes. In addition, there is a lack of well-designed cost-effectiveness studies using standard methods. The BICAT-NL study will provide more insight in refractive and cost-effectiveness outcomes for ISBCS compared to DSBCS.

### Study status

Currently, recruitment of patients is on-going. Recruitment has started on the 4th of September 2018 and is expected to be completed by August 2020. The latest version of the study protocol is version 7.0 (date: 02-08-2019).

## Data Availability

This manuscript does not contain any data or results. Therefore, data sharing is not applicable.

## Abbreviations

BIA: Budget impact analysis
CDVA: Corrected Distance Visual Acuity
CRF: Case Report Form
CTCM: Clinical Trial Center Maastricht
DSBCS: Delayed Sequential Bilateral Cataract Surgery
ETDRS: Early Treatment Diabetic Retinopathy Study
GCP: Good Clinical Practice
HRQL: Health-related Quality of Life
HUI-3: Health Utility Index Mark 3
ICER(s): Incremental cost-effectiveness ratio(s)
ISBCS: Immediately Sequential Bilateral Cataract Surgery
LogMAR: Logarithm of the Minimum Angle of Resolution
NEI VFQ-25: National Eye Institute Visual Function Questionnaire-25
PROM(s): Patient Reported Outcome Measure(s)
QALY(s): Quality Adjusted Life Year(s)
RCT: Randomised Controlled Trial
